**Methods:**

The D2 study is a single centre, observational, longitudinal case control study that will follow 168 adult patients aged >50 years with type 2 diabetes: 50% with LVH (case) and 50% without LVH (control). It will assess change in cardiovascular risk, brain imaging and neuropsychological testing between two time-points, baseline (0 months) and 24 months. The primary outcome is brain volume change at 24 months. The co-primary outcome is the presence of cognitive decline at 24 months. The secondary outcome is change in left ventricular mass associated with brain atrophy and cognitive decline at 24 months.

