### Study outcome measures

Our primary endpoint is brain volume change at 2 years (hypothesis 1). Our co-primary outcome is the presence of cognitive decline at 2 years (hypothesis 2). We shall use advanced brain imaging to accurately measure brain volume and correlate this with cardiac echocardiography, carotid intima media thickness (CIMT), and 24 h blood pressure and ECG monitoring in 168 patients with type 2 diabetes, with longitudinal testing allowing measurement of change at 24 months. Concurrent neuropsychological testing will indicate whether the clinical profile of cognitive impairment and dementia aligns with measures of brain volume.

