### Eligibility criteria

Inclusion criteria are as follows: (1) aged over 50 years; (2) no prior neurological or psychiatric disease, including stroke; (3) ability to give informed consent and participate in cognitive testing. The study exclusion criteria are as follows: (1) known prior stroke, transient ischemic attack or dementia; (2) significant medical co-morbidities precluding participation in cognitive testing, or making survival for 24 months unlikely; (3) normal exclusion criteria for MRI; e.g., implanted metal, severe claustrophobia; (4) severe diabetic nephropathy: estimated glomerular filtration rate (eGFR <30 mL/min/1.73 m^2^).

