### Sample size

We aim to recruit 168 patients with type 2 diabetes. Patients will be divided based on the presence of LVH. Higher left ventricular mass and concentric geometric changes have been demonstrated in approximately 35–40% of patients with type 2 diabetes [16, 17]. Our data suggested more than 50% of participants will have LVH [18]. We calculated our sample size in order to include sufficient participant numbers for both the primary endpoint comparison (brain volume) and for the primary outcome measure (presence of cognitive impairment). The primary endpoint requires a direct comparison of two groups: type 2 diabetes patients with LVH and those without. We based our effect size on published brain volume and cortical thickness estimates performed on healthy controls, cerebrovascular disease patients and Alzheimer’s disease patients [40–42], and prior imaging of healthy controls and stroke patients performed by our group [43]. We use an average brain volume change of <0.5% per annum for controls, 1–2% for cerebrovascular disease, and 2–4% for dementia [44].

We used a modified retrospective case-control method. All participants have the exposure (type 2 diabetes), which will naturally halve by the additional risk factor (LVH, expected prevalence around 50%), but only some of them will develop the primary outcome (cognitive decline). We used an ANCOVA method to estimate sample size for four samples (cognitively impaired LVH, non-cognitively impaired LVH, cognitively impaired non-LVH, non-cognitively impaired non-LVH) with repeated measures, including a correlation score between baseline and follow-up. Using alpha = 0.05 (two-sided), power = 0.8 and an estimated correlation of 0.1, we estimated that 140 (i.e., 35 in each of 4 groups) participants will be required. Given we expect around 20% attrition due to death or non-participation (unable to participate in testing due to new pacemaker/implanted metal/other medical issue, lost to contact, no longer interested), we have estimated a total recruitment number of 168. This model has used the conservative estimates from these results and assumes the following: that 30% of patients will be cognitively impaired at 2 years; a 1% total annual brain volume change for patients with type 2 diabetes; that 30% of patients will exhibit specific left ventricular geometric changes; and a low correlation between baseline and follow-up measures.

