### Statistical analysis

The analysis of this study will be performed in three parts as follows.
***Hypothesis 1: comparing brain volumes between participants with and without LVH***. Independent samples t-tests will be used to determine differences between participants with and without LVH at each time-point. Repeated-measures t-tests will be used to determine the extent of brain volume loss across the two time-points. These results will be compared between groups. In the cortical thickness analyses, the large number of statistical inferences being carried out across the cortical sheet (approximately 160,000 vertices per hemisphere) requires adjustment of the statistical threshold. This is to control for the increased number of false positive findings using false discovery rate correction procedure widely used for cortical thickness analyses. In the volumetric analyses, total brain volume, regional white matter, cortical and subcortical volume changes will be modelled using a repeated measures design. Intracranial volume, which is determined partially by gender and race, is a known confounding factor that contributes to regional brain volumes. This will be controlled for in the statistical analysis of regional brain volume change. We have demonstrated this to be a reliable index of brain volume in previous studies [43].
***Hypothesis 2: correlating brain volume with cognitive performance.*** The initial regressive analysis will examine differences between cognitively impaired and normal participants at 2 years. We will correlate both global and regional measures of brain volume with the groups. Global brain and regional hippocampal volumes, and mean regional cortical thickness values for the stated regions of interest will be compared between two groups, in order to correlate LVH-associated brain volume changes with cognition. We will also perform a multivariate analysis across the cohort as a whole to investigate whether there is a dose-related association with any extent of cardiac impairment. Multivariate regression will be conducted to determine whether brain volume loss correlates with the presence or absence of cognitive impairment, adjusting for known important variables such as age, years of education, CIMT, atrial fibrillation, cholesterol and hypertension, as well as potentially relevant variables including *APOE* ε4 status, cardiac indices such as stroke volume, renal function and HbA_1c_ levels.

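### The co-primary outcome is cognitive decline, but its analysis and planning rate use impairment status at 2 years, which is a different quantity

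*Protocol article*

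**What the plan says.** **Outcome as defined.** The Abstract (Methods) states: "The co-primary outcome is the presence of cognitive decline at 24 months". The section Study outcome measures repeats this and ties it to a hypothesis: "Our co-primary outcome is the presence of cognitive decline at 2 years (hypothesis 2".

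**Outcome as analysed.** Under Hypothesis 2 in Statistical analysis, the first step is: "The initial regressive analysis will examine differences between cognitively impaired and normal participants at 2 years". The adjusted analysis follows: "Multivariate regression will be conducted to determine whether brain volume loss correlates with the presence or absence of cognitive impairment". Age, education, CIMT, atrial fibrillation, cholesterol, hypertension, *APOE* ε4, cardiac indices, renal function and HbA1c are named as adjustment variables. Baseline cognition is not named.

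**Outcome as planned for.** The Sample size section uses two names for one outcome. It refers to numbers "for the primary outcome measure (presence of cognitive impairment" and later says that "only some of them will develop the primary outcome (cognitive decline". Its rate assumption is "that 30% of patients will be cognitively impaired at 2 years".

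**Who can enter.** Eligibility criteria exclude "known prior stroke, transient ischemic attack or dementia", require no earlier neurological or psychiatric illness, and require the ability to take part in cognitive testing. No cognitive score threshold is set. The Abstract's Background describes cognitive impairment as common in this population.

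**What is measured.** Table 1 schedules the cognitive battery at both 0 and 24 months.

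**The concern.** Decline needs two measurements on the same person; impairment status needs one. The two classifications agree only if nobody is impaired at entry and everyone who declines crosses the impairment threshold. The protocol secures neither condition. A participant impaired at both visits, with no change between them, falls in the impaired group. A participant who falls substantially from a high starting level but stays within norms falls in the normal group.

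What is at stake is the meaning of the co-primary result. A link between brain volume loss and status at 2 years could partly reflect impairment that predates the study, yet it would be reported under the label of decline. Real associations with decline could equally be blurred by the misgrouping. The direction cannot be settled from the document.

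**Working it through.** **1. The plan's own figures.** The Sample size section gives 35 in each of 4 groups, so 4 × 35 = 140 evaluable. The 140 cannot be re-derived, because the ANCOVA calculation states no effect size in SD units and no SD. The point here does not depend on that derivation; it uses only the 140 and the 30%.

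**2. Expected impaired group.** 0.30 × 140 = 42 participants impaired at 2 years.

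**3. How many would be new.** Let *b* be the proportion impaired at baseline who remain impaired. The document gives no value for *b*, so it is an assumption, shown as a range.

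- Already impaired = 140 × *b*
- New cases = 42 − 140 × *b*
- Share of the impaired group that is not new = *b* / 0.30
- New impairment among those unimpaired at baseline = (0.30 − *b*) / (1 − *b*)

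| Assumed *b* | Already impaired | New cases | Share of the 42 not new | New impairment among the unimpaired |
|---|---|---|---|---|
| 0% | 0 | 42 | 0% | 30.0% |
| 5% | 7 | 35 | 17% | 26.3% |
| 10% | 14 | 28 | 33% | 22.2% |
| 15% | 21 | 21 | 50% | 17.6% |
| 20% | 28 | 14 | 67% | 12.5% |

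Only at *b* = 0 do impairment at 2 years and new impairment coincide.

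**4. Does another section repair it?** The Hypothesis 3 text in Statistical analysis mentions longitudinal analysis, but the paired test it names is for brain volume, and it refers cognition back to the methods already described for Hypothesis 2. The cognitive assessment section standardises test scores to norms and averages them into domain scores, but gives no rule for decline or impairment. No section removes participants impaired at baseline from the impaired group or says that baseline cognition is accounted for.

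The table covers only the first error, prevalent cases counted with decliners. The second, decline within the normal range, cannot be sized even by illustration, because no cut-off or score distribution is given.

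**The case against.** The strongest reply is that this is loose wording. The Sample size section speaks of participants who go on to develop the outcome and describes a repeated-measures ANCOVA with a baseline-to-follow-up correlation. Both suggest that new cases were meant and that impaired at 2 years is shorthand for newly impaired. An article may also leave the cut-off and the handling of baseline cases to a fuller document. Hypothesis 2 itself is worded as an association of atrophy with worse cognitive performance, which a status comparison can address.

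Some of this stands. Intent is ambiguous, and a missing cut-off alone would be no finding. But the article does more than omit a detail: it names one outcome and writes down the analysis of another. A later plan that followed either text would depart from the other.

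Four stronger readings are tempting and are not supported:

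- *That a given loss of power or inflated false-positive rate follows.* Such figures can be produced by comparing impairment proportions between LVH groups under assumed rates of decline and baseline impairment. The document gives none of those rates, and that is not the Hypothesis 2 test, which relates brain measures to impairment.
- *That known dementia is the only cognitive safeguard at entry.* The criteria also exclude stroke, TIA and earlier neurological or psychiatric illness. This should lower baseline impairment, but it does not reach mild or undiagnosed cases.
- *That baseline cognition is ruled out of the model.* The covariate list is open-ended. Baseline cognition is not named, but it is not barred.
- *That the sample size was built on status alone.* That section uses both terms.

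**Conclusion.** The mismatch is established from the text: a change outcome is defined, and a single-visit status is analysed and used for the planning rate. Taken as written, people already impaired at entry are grouped with decliners, and decliners who stay within norms are grouped as normal.

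The size is unknown. The 17% to 67% range is an illustration. It rests on the protocol's 140 and 30%, on an assumed baseline prevalence of 5% to 20%, and on those people remaining impaired at 24 months. Recovery to normal by 24 months, or a lower prevalence because of the exclusions, would reduce it. The conclusion that the co-primary as defined has no matching analysis does not depend on any of these assumptions.

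**What to change.** - Choose one definition of the co-primary that uses the cognitive scores from both visits, and state it in advance. Several are defensible, for example a reliable-change rule applied to the domain scores, or new impairment among those unimpaired at baseline.
- Use that variable in both Hypothesis 2 analyses (the group comparison and the adjusted regression), and use one term for it in the Abstract, Study outcome measures, Sample size and Statistical analysis.
- Say explicitly how baseline cognition enters. Adjusting a change outcome for the baseline score is itself debatable here, because LVH may already have affected cognition before entry, so the choice should be reasoned.
- Restate the 30% as a rate of the chosen outcome.
- Keep impairment status at 24 months as a secondary outcome, with those impaired at baseline shown separately.

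The cost is wording and one derived variable; no new data are needed, since the battery is already scheduled at both visits. The drawback is that the rate of decline is likely to be below 30%, so the planning figure becomes less favourable. In the illustration, new impairment among those unimpaired at baseline falls to between 26.3% and 12.5%.

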### Study hypotheses

Patients with type 2 diabetes and LVH will exhibit greater brain atrophy as assessed by MRI structural changes than those without LVH.Brain atrophy as assessed by MRI structural changes will be associated with worse cognitive performance.Increased left ventricular mass with specific left ventricular geometric patterns will be associated with the most severe regional brain atrophy and cognitive decline.

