#### Carotid Doppler ultrasound

CIMT measurements will be conducted in the Neurology diagnostics laboratory, Austin Health by a single technician. High-resolution B-mode ultrasound images will be obtained on both right and left internal carotid arteries. CIMT will be measured, and the degree of stenosis will also be classified into accepted clinical grades for incorporation into multivariate analyses: none, <50%, 50–69%, 70–79%, 80–89%, 90–99% and occluded (NASCET criteria) [32].

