#### Cognitive and mood assessment questionnaire and tests

Participants will complete a neuropsychological assessment. The assessment will include several paper-and-pencil and computerized cognitive tasks and mood questionnaires. Six cognitive domains will be examined, including (i) attention, (ii) visuospatial ability, (iii) executive function, (iv) language, (v) memory, and (vi) processing speed. The tasks used to measure each cognitive domain are listed in Table 2. This protocol has been modelled on that validated by the CANVAS study, a longitudinal study of patients after stroke [36]. All tasks are designed for serial testing and are less affected by practice effects. Performance on individual cognitive tests will be standardised using established norms and domain scores will be calculated by averaging the standardised scores from each contributing test (e.g., Trail Making Test as a measure of attention). Assessment of mood will be completed using the seven-item Generalized Anxiety Disorder (GAD-7) questionnaire and the nine-item Patient Health Questionnaire (PHQ-9). These questionnaires are based on criteria for the diagnosis of generalised anxiety and depression (Diagnostic and Statistical Manual-Fourth Edition: DSM-V) [37].

**Table 2 Tab2:** Tasks used to measure each cognitive domain

Cognitive domain	Cognitive task
Global Cognitive Ability	Montreal Cognitive Assessment [45]
	The Clinical Dementia Rating [46]
	National Adult Reading Task [47]
Attention	Trail-Making Test [48]
	Digit Span Task (WAIS-IV) [49]
	Identification Task (Computerised CogState battery) [50]
	One Back Task (Computerised) [50] CogState battery)
Visuospatial Ability	Rey Complex Figure Test (Copy) [51]
Executive Function	Clock Drawing Task – CLOX [52]
	Controlled Oral Word Association Test [53]
Language	30-item Boston Naming Test [54]
	Verbal Fluency Test [53]
Memory	Rey Auditory Verbal learning Task [55]
	Rey Complex Figure Test (Recall) [51]
Processing Speed	Detection Task (Computerized CogState battery) [50]
	Digit-Symbol Task (WAIS-IV) [49]

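### Hypothesis 2 concerns graded cognitive performance, but its specified analyses use only impaired versus normal; a continuous-score regression should be added beside the binary co-primary analysis

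*Protocol article*

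**What the plan says.** **The hypothesis (Study hypotheses).** It is stated in graded terms: "Brain atrophy as assessed by MRI structural changes will be associated with worse cognitive performance". The Hypothesis 2 heading under Statistical analysis also refers to cognitive performance.

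**The outcome (Study outcome measures).** The outcome tied to this hypothesis is binary: "Our co-primary outcome is the presence of cognitive decline at 2 years (hypothesis 2".

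**The data (Cognitive and mood assessment).** Each test is standardised against norms, and "domain scores will be calculated by averaging the standardised scores from each contributing test". Table 1 schedules the cognitive evaluation at both 0 and 24 months, so scores will exist at both visits.

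**The analysis (Statistical analysis, Hypothesis 2).**
- The first step is a comparison of groups: "The initial regressive analysis will examine differences between cognitively impaired and normal participants at 2 years".
- Global and regional volumes are then related to those groups.
- The adjusted regression is to "determine whether brain volume loss correlates with the presence or absence of cognitive impairment". It is to be fitted "adjusting for known important variables such as age, years of education, CIMT, atrial fibrillation, cholesterol and hypertension", followed by a second list of possibly relevant variables: APOE ε4 status, "cardiac indices such as stroke volume, renal function" and HbA1c.

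**The planning assumption (Sample size).** It assumes that 30% of patients will be cognitively impaired at 2 years.

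**The concern.** The hypothesis asks whether more atrophy goes with worse performance. The specified analyses ask whether atrophy differs between two classes. Splitting a score into impaired and normal treats everyone on the same side of the cut as equal: a participant just below it counts the same as one far below it. The scores that would separate them are already to be computed.

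What is at stake is power for the atrophy-cognition association. A real association of modest size could be missed, and the null result could be read as evidence against the hypothesis, when the loss came from the coding of the outcome.

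This is not a detail that an article simply leaves to a fuller plan. The article does state how cognition enters the Hypothesis 2 analyses, and that form does not match the hypothesis as worded.

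**Working it through.** **Step 1. Is the continuous score used anywhere against brain volume?**
- Hypothesis 2, initial analysis: impaired versus normal.
- Hypothesis 2, volumes and cortical thickness: compared between two groups.
- Hypothesis 2, dose-related analysis: grades the extent of cardiac impairment, not cognition.
- Hypothesis 2, adjusted regression: presence or absence of impairment.
- Hypothesis 3, multiple regression: relates cognitive and brain volume measures to left ventricular mass, not to each other. Its correlation with cognition refers back to the Hypothesis 2 methods.

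No stated analysis relates brain volume change to the continuous scores.

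**Step 2. Evaluable numbers.** The article gives no planned power for this association, so there is no figure of its own to reproduce here. It requires 140 participants and recruits 168, which is 140 × 1.2. After 20% attrition, 168 × 0.8 = 134.4 remain. I use 134 to 140.

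**Step 3. Information kept after a single cut.** For a normally distributed score with proportion p below the cut, and a modest association, the relative efficiency is φ(z_p)² / [p(1 − p)].
- With p = 0.30: |z| = 0.524, φ(0.524) = 0.3477, and 0.3477² / 0.21 = 0.576.
- Information lost: 1 − 0.576 = 0.424, or about 42%.
- Effective numbers: 134 × 0.576 = 77; 140 × 0.576 = 81.
- The correlation shrinks by √0.576 = 0.76.

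| Proportion impaired | Efficiency | Information lost |
|---|---|---|
| 20% | 0.490 | 51% |
| 25% | 0.539 | 46% |
| 30% | 0.576 | 42% |
| 40% | 0.622 | 38% |
| 50% | 0.637 | 36% |

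**Step 4. Power.** The documents give no brain-cognition correlation, so r is assumed. With two-sided α = 0.05, power ≈ Φ(atanh(r)·√(n − 3) − 1.96). For n = 134, √131 = 11.446.
- r = 0.25, continuous: 0.2554 × 11.446 − 1.96 = 0.96, power 83%.
- r = 0.25, binary (r becomes 0.25 × 0.759 = 0.190): 0.1920 × 11.446 − 1.96 = 0.24, power 59%.
- r = 0.20, by the same route: 64% continuous, 42% binary.

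A simulation with n = 140, ten independent covariates and 2,000 runs compared the two ways of fitting the binary version:

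| True r | Continuous score | Binary, linear (brain volume as outcome) | Binary, logistic |
|---|---|---|---|
| 0.20 | 62% | 39% | 42% |
| 0.235 | 77% | 54% | 56% |
| 0.30 | 94% | 74% | 75% |

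The loss appears whichever variable is taken as the outcome.

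**Step 5. Covariate load.** The first list names six variables and the second four. With brain volume loss that makes 11 terms. Expected impaired participants: 0.30 × 134 = 40, or 0.30 × 140 = 42. Per term: 40.2 / 11 = 3.7, or 42 / 11 = 3.8. This ratio matters only if impairment is the outcome of a logistic model. If brain volume loss is the outcome of a linear model, the ratio is 134 / 11 = 12 participants per term.

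**The case against.** **The binary form has a declared basis.** Study outcome measures names the presence of cognitive decline as co-primary and ties it to Hypothesis 2, and the sample size is built on impaired and non-impaired groups. This stands. A reader might infer that the binary analysis is a mistake to be replaced or made secondary. The documents do not support that: demoting it would change a declared outcome as well as the analysis text.

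**The 42% depends on assumptions.** It requires one roughly normal score cut at one threshold. The article lists six domains as well as the Montreal Cognitive Assessment and the Clinical Dementia Rating, and does not say how impaired is derived. For a multi-domain or clinical classification the formula is only approximate. This also stands, so the figure must be given as conditional and with its range.

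**Overfitting is not established.** A reader might infer that the adjusted model is a logistic regression with too few impaired participants. The Hypothesis 2 text does not name the dependent variable, and logistic regression is mentioned only under Hypothesis 3. The covariate lists are open-ended and may be candidates, not a fixed set. About four impaired participants per term is therefore a conditional warning. Nor can the seven carotid stenosis grades be counted as extra terms: they are meant for unspecified multivariate analyses, while the Hypothesis 2 list names CIMT.

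**A continuous analysis may be intended.** The group comparison is called initial, and the heading speaks of performance. But the adjusted regression that follows is explicitly binary, so this does not remove the mismatch.

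**Conclusion.** The point holds as a mismatch between Hypothesis 2 as worded and the analyses specified for it. The scores that would test it directly are already planned, yet nothing in the article relates them to brain volume loss.

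The cost is about 42% of the information at the protocol's own 30% impaired, and 36% to 51% for 50% to 20% impaired. At an assumed correlation near 0.25, that takes power from about 83% to about 59%. These sizes rest on a single cut of a roughly normal score and on a correlation that the documents do not give. The direction of the loss does not depend on which variable is the outcome.

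The finding does not make the binary co-primary analysis wrong, and it does not show that the adjusted model is overfitted.

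**What to change.** Keep the impaired/normal analysis for the co-primary outcome. Add to the Hypothesis 2 paragraph of Statistical analysis, as the test of the hypothesis as worded:

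- a linear regression of the 24-month continuous cognitive score on percentage brain volume loss from 0 to 24 months, adjusted for the baseline score;
- a statement of which score carries the test. The mean of the six domain scores gives one test but must be defined, since the article defines only domain scores. If the domain scores are tested separately, state how multiplicity is handled;
- a short, fixed covariate list drawn from the variables already named, for example age, years of education, hypertension and APOE ε4 status;
- the dependent variable of the existing binary regression. If it is impairment in a logistic model, the ratio of about four impaired participants per term is a further reason to use the short list there too.

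The cost is one more prespecified analysis and some wording; no new data or visits are needed. The drawback is that a score difference is less directly clinical than impaired versus normal, which is another reason to report both.

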#### Transthoracic echocardiography (TTE)

TTE will be performed by a cardiologist using a commercially available portable ultrasound system (Vivid i, GE Healthcare). Standard parasternal and apical views will be used to assess left ventricular mass. Measurements are obtained according to the American Society of Echocardiography (ASE) recommendations [31]. M-mode echo will be used to measure cardiac dimensions and wall thickness. Ejection fraction will be calculated using the modified Simpson’s rule. Left ventricular mass will be indexed using the ASE corrected convention, by dividing left ventricular mass by height^2.7^. LVH will be defined as >49 g/m^2.7^ for males and >45 g/m^2.7^ for females. Relative wall thickness will be calculated, and left ventricular remodelling classified as normal, eccentric, or concentric remodelling and concentric LVH.

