***Hypothesis 3: comparing brain volume and cognitive performance in participants with increased left ventricular mass and specific left ventricular geometric patterns.*** Analysis will be similar to that for LVH, except that patients will be divided on the presence or absence of specific morphometric measures. That is, analyses will be performed at each time-point (cross-sectional), and also longitudinally, to investigate change across time. Repeated-measures t-tests will determine the extent of brain volume loss across the two time-points and compared between groups. Correlation with cognitive performance will be performed as above. Unadjusted differences for clinical variables between groups will be assessed by *t*-test. Difference in laboratory data and left ventricular systolic function will be adjusted for age and sex by use of ANCOVA. Differences in left ventricular structure and geometry will be adjusted for age, sex, BMI, and systolic blood pressure as their major established covariates with further adjustment for duration of hypertension. Fisher’s Exact Test and odds ratios will be used to test differences for categorical variables. Logistic regression analysis will be used to derive odds ratios adjusted for covariates. Multiple regression analyses will be performed to assess relation of cognitive and brain volume measures to higher left ventricular mass independent of established covariates and duration of hypertension.

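### Hypothesis 3 is about which LV geometry goes with the most severe atrophy, but its present/absent split cannot rank the patterns and can confound a pattern with LVH, in a direction that depends on the pattern

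*Protocol article*

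**What the plan says.** All references are to the protocol article.

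- **Study hypotheses**, third hypothesis: "Increased left ventricular mass with specific left ventricular geometric patterns will be associated with the most severe regional brain atrophy and cognitive decline".
- **Transthoracic echocardiography (TTE)**: relative wall thickness is calculated and "left ventricular remodelling classified as normal, eccentric, or concentric remodelling and concentric LVH". LVH itself is a mass criterion: "LVH will be defined as >49 g/m^2.7^ for males and >45 g/m^2.7^ for females".
- **Statistical analysis**, Hypothesis 3, the grouping rule: "Analysis will be similar to that for LVH, except that patients will be divided on the presence or absence of specific morphometric measures". The groups are then compared cross-sectionally at each visit and longitudinally by t-tests.
- **Statistical analysis**, Hypothesis 3, the models: "Multiple regression analyses will be performed to assess relation of cognitive and brain volume measures to higher left ventricular mass independent of established covariates", and "Differences in left ventricular structure and geometry will be adjusted for age, sex, BMI, and systolic blood pressure as their major established covariates", with duration of hypertension added.
- **Sample size**: "LVH, expected prevalence around 50" per cent, and the assumption "that 30% of patients will exhibit specific left ventricular geometric changes".

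**The concern.** The hypothesis makes a claim of degree among patterns. The echocardiography section supplies more than two classes, some of them LVH by mass and some not. The stated analysis reduces these classes to a two-way split, pattern against all others. Two problems follow.

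1. A difference from the average of the rest does not show that a pattern is the worst, because one class inside the rest may be worse still.
2. The comparison group generally has a different share of LVH patients from the pattern group. If LVH affects brain volume, which is Hypothesis 1, part or all of that effect can reappear under Hypothesis 3 as if it belonged to the geometry.

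At stake is how a Hypothesis 3 result is read. A positive finding could be the LVH result seen a second time, and a protective-looking finding could be an artefact of the reference group.

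**Working it through.** **Inputs from the Sample size section.** LVH prevalence about 50%; specific geometry 30%; 140 evaluable patients (4 × 35); two-sided alpha 0.05; power 0.8. The plan gives no figure for a pattern contrast. It also states no between-group difference and no SD, so 140 cannot be rebuilt from its inputs and is used here only as N.

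**Assumptions.** D is the difference in brain volume loss between LVH and non-LVH patients, in SD units. It is not stated, so a range is shown. The pattern is given no effect of its own. The article does not say how the 30% divides between LVH and non-LVH patients, so several cases are shown.

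**Bias.** Apparent effect = D × [P(LVH | pattern) − P(LVH | no pattern)].

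| Where the 30% lies | LVH share, pattern present | LVH share, pattern absent | Apparent effect |
|---|---|---|---|
| Wholly within LVH (e.g. concentric LVH) | 30/30 = 100% | (50 − 30)/70 = 28.6% | +0.71 D |
| 20 points within, 10 outside | 20/30 = 66.7% | 30/70 = 42.9% | +0.24 D |
| Equally common in both (15 and 15) | 15/30 = 50% | 35/70 = 50% | 0 |
| Wholly outside LVH (e.g. concentric remodelling) | 0% | 50/70 = 71.4% | −0.71 D |

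At 40% LVH the extremes are 1 − 10/70 = +0.86 D and −40/70 = −0.57 D. At 55% LVH they are 1 − 25/70 = +0.64 D and −55/70 = −0.79 D.

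**How often an inert pattern is declared significant.** First case, N = 140, so 42 with the pattern and 98 without (normal approximation):

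| D (SD) | Apparent effect (SD) | Rejection rate |
|---|---|---|
| 0 | 0 | 5% |
| 0.2 | 0.14 | 12% |
| 0.3 | 0.21 | 21% |
| 0.474 | 0.34 | 44% |
| 0.67 | 0.48 | 73% |

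The value 0.474 is what 70 versus 70 detects with 80% power: (1.96 + 0.842) × √(2/70) = 0.474. The value 0.67 is the same quantity for 35 versus 35. In 10,000 simulated trials at D = 0.474, the split rejected 43.5% of the time in the first case, essentially always in the harmful direction. For a pattern wholly outside LVH it rejected 43.0%, essentially always in the protective direction. A contrast within the same LVH stratum rejected 4.7% and 4.8%, with a mean estimate of about 0.00.

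**Ranking.** Suppose the 30% is all concentric LVH with excess loss c > 0, the other 20 points of LVH are another class with excess loss e, and non-LVH patients have none. The split estimates c − (20/70)e. This stays positive until e = 3.5c (70/20). The split can therefore favour concentric LVH while the other LVH class loses more.

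**Do other stated models repair this?** The multiple regression takes LV mass as the exposure, not pattern given mass. The ANCOVA statements treat LV structure and geometry as outcomes, and LVH is not a listed covariate. The regression under Hypothesis 2 cites stroke volume as its example of a cardiac index, not LVH. The adjusted logistic regression names no covariates. None compares patterns with one another.

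**The case against.** The article does not define the morphometric measures, and such detail may sit in an analysis plan that is not shown. A split on raised relative wall thickness could cut across LVH with little or no bias. Hypothesis 3 joins mass and pattern, so comparing that combined phenotype with everyone else is a legitimate reading. The split is also not the only planned analysis, since regressions on LV mass and a whole-cohort multivariate analysis are stated too.

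Much of this stands, and it rules out several stronger inferences a reader might draw:

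- *An inert pattern will look harmful.* Only if LVH has a real effect and the pattern is commoner within LVH. Otherwise it may look protective or be unbiased.
- *The second study aim cannot be answered.* That aim asks for association between geometric measures and brain volume change, which a two-way split can test.
- *A true pattern effect is diluted by LVH patients in the reference.* With own effect P and the pattern wholly within LVH, the contrast is (P + D) − 0.286 D = P + 0.71 D. For D > 0 this overstates P.
- *Hypothesis 1 is contaminated by non-LVH patients with abnormal geometry.* Hypothesis 1 compares LVH with no LVH, defined by mass, so those patients belong to its stated comparator. The article gives no prevalence of such geometry among them.

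Two things survive. The grouping rule is affirmatively stated, so this is not a matter of omitted detail. And no stated model compares patterns with each other or names LVH or LV mass as a covariate for pattern.

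**Conclusion.** The concern holds in a limited form. As written, the Hypothesis 3 split cannot support a claim that one pattern goes with the most severe atrophy, and it can confound pattern with LVH. With 50% LVH and 30% pattern, the bias for an inert pattern runs from about −0.71 D to about +0.71 D according to how the pattern overlaps with LVH, and is zero when it is equally common in both groups. The bias vanishes if LVH has no effect. The size rests on the plan's two prevalences, an unstated D and an unstated overlap. The primary and co-primary outcomes are tied to Hypotheses 1 and 2, so this affects a non-primary hypothesis. It is worth correcting because the classes are already being measured.

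**What to change.** In the Hypothesis 3 paragraph of Statistical analysis, enter the geometry classes from the echocardiography section as one factor, with normal geometry as the common reference. Pre-specify a contrast between patterns within LVH patients, or a pattern effect adjusted for LV mass, and report it as an estimate with its confidence interval. The present/absent comparison may stay as a description of association.

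The change needs no new data. The cost is precision. If the 30% pattern lies within LVH, N = 140 gives 70 LVH patients, of whom 42 have the pattern and 28 do not. The standard error is √(1/42 + 1/28) = 0.244 SD, so the detectable difference at 80% power is 2.80 × 0.244 = 0.68 SD, and power for 0.474 SD is about 49%. A non-significant contrast should therefore not be read as showing that the patterns are equivalent.
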